## Abstract

**Background:**

Risk factors, such as the number of pre-existing co-morbidities, the extent of the underlying pathology and the magnitude of the required operation, cannot be changed before surgery. It may, however, be possible to improve the cardiopulmonary fitness of the patient with an individualised exercise program. We are performing a randomised controlled trial (RCT) assessing the impact of High Intensity Interval Training (HIIT) on preoperative cardiopulmonary fitness and postoperative outcomes in patients undergoing major abdominal surgery.

**Methods:**

Consecutive eligible patients undergoing elective abdominal surgery are being randomised to HIIT or standard care in a 1:1 ratio. Participants allocated to HIIT will perform 14 exercise sessions on a stationary cycle ergometer, over a period of 4–6 weeks before surgery. The sessions, which are individualised, aim to start with ten repeated 1-min blocks of intense exercise with a target of reaching a heart rate exceeding 90% of the age predicted maximum, followed by 1 min of lower intensity cycling. As endurance improves, the duration of exercise is increased to achieve five 2-min intervals of high intensity exercise followed by 2 min of lower intensity cycling. Each training session lasts approximately 30 min. The primary endpoint, change in peak oxygen consumption (Peak VO_2_) measured during cardiopulmonary exercise testing, is assessed at baseline and before surgery. Secondary endpoints include postoperative complications, length of hospital stay and three clinically validated scores: the surgical recovery scale; the postoperative morbidity survey; and the SF-36 quality of life score. The standard deviation for changes in Peak VO_2_ will be assessed after the first 30 patients and will be used to calculate the required sample size.

**Discussion:**

We want to assess if 14 sessions of HIIT is sufficient to improve Peak VO_2_ by 2 mL/kg/min in patients undergoing major abdominal surgery and to explore the best clinical endpoint for a subsequent RCT designed to assess if improving Peak VO_2_ will translate into improving clinical outcomes after surgery.

**Trial registration:**

Australian New Zealand Clinical Trials Registry, ACTRN12617000587303. Registered on 26 April 2017.

## Background

While complications continue to be a common event after abdominal surgery [1], the ability to predict who will develop perioperative complications remains difficult because the aetiology of adverse events is multifactorial [2]. In terms of reducing the likelihood of complications, many of the most important risk factors—such as the number of pre-existing co-morbidities, the extent of the underlying pathology and the magnitude of the required operation—cannot be changed before surgery. Stopping smoking [3] and optimising specific medical problems will improve the outcome in some patients. However, one important risk factor which it may be possible to improve in a significant group of patients is the functional reserve or the cardiopulmonary fitness of the patient.

Cardiopulmonary fitness can be assessed by measuring oxygen consumption during cardiopulmonary exercise testing (CPET). We know that this is an important clinical measurement as a poor oxygen consumption, including an anaerobic threshold (AT) of < 10-11 mL/kg/min [4–6] or a peak oxygen consumption (Peak VO_2_) of < 15–18.6 mL/kg/min [7], has been demonstrated to be associated with significantly higher rates of postoperative complications. In general terms, a low oxygen consumption is also predictive of a higher medium-term mortality risk [8], and it has been estimated that approximately half of patients presenting for intra-abdominal surgery do not have the prerequisite fitness on objective exercise testing to be considered at low risk for postoperative complications [9].

The main types of aerobic exercise which may improve oxygen consumption are High Intensity Interval Training (HIIT) and continuous moderate exercise. General studies (not perioperative) comparing the impact of these different types of exercise have shown that HIIT results in a more substantial [10] and faster [11, 12] improvement in Peak VO_2_ than continuous moderate exercise. The faster improvement is important in the context of surgery, as the urgency of the required surgery may mean that there is a limited period of time available between the time of diagnosis and surgery. There is also some evidence that a supervised HIIT program is safe in patients with moderate coronary artery disease and cardiac failure [12].

Although the general benefits of exercise have been widely studied and there is an increasing literature on the benefits of preoperative exercise, there are a number of important questions that need to be answered. Studies in the literature can be classified into four groups: (1) those that look at multimodal prehabilitation interventions including physical exercises (which may include muscle strengthening, aerobic and respiratory exercises), nutritional supplementation and psychological support; (2) those that assess aerobic exercises but do not measure oxygen consumption; (3) those that assess the impact of aerobic exercises on oxygen consumption; and (4) those that assess at the impact of HIIT on oxygen consumption. A review of prehabilitation [13] assessing the role of muscle strengthening, respiratory and aerobic exercises in orthopaedic, cardiac and abdominal surgery highlighted the potential of two weeks of inspiratory muscle training to reduce respiratory complications and to potentially reduce length of stay after cardiac and abdominal surgery. A recent review of prehabilitation, which identified nine studies using aerobic exercises before abdominal cancer surgery [14], consistently showed some improvements in the distance walked over 6 min or in oxygen consumption. However, only two of four studies found evidence that the quality of life was improved, only one of three found evidence that patient anxiety was decreased, and there was no identified reduction in postoperative complications. The main conclusion of this review was that the significant heterogeneity in almost all aspects of the identified studies made it difficult to come to any firm conclusions. They emphasised the need for greater standardisation in future studies.

We have identified ten studies that document the impact of preoperative aerobic exercise on either the anaerobic threshold or Peak VO_2_ in the 4–6 weeks before surgery [15–24]. All studies were on patients undergoing major abdominal or thoracic procedures. All except one [22] demonstrated an improvement in oxygen consumption. Two recent studies have prospectively assessed the impact of HIIT. In 2015, West et al. [15], in a non-randomised study which included 22 patients having 18 sessions of HIIT over six weeks after long course chemoradiotherapy for rectal cancer, demonstrated a 2.65 mL/kg/min recovery of maximal oxygen consumption back to the pre-chemoradiotherapy levels of oxygen consumption. In 2016, Dunne et al. [18], in a randomised study which included 19 patients having 12 sessions of HIIT over four weeks before liver surgery, demonstrated a 2.0 mL/kg/min improvement in Peak VO_2_. While the majority of studies assessing the impact of aerobic exercise on cardiopulmonary fitness have demonstrated an improvement in oxygen consumption [15–21, 23, 24], these studies have a number of limitations. All but one [19] had a small sample size, with 26 or less patients being exercised. Only three studies were randomised [18–20], only one prospectively assessed postoperative complications in a systematic way [19] and only two based their exercise program around the principles of HIIT [15, 18]. In this context there continues to be a need for well-designed randomised studies to confirm the extent of the impact of preoperative HIIT on oxygen consumption and to further assess what an optimal preoperative program of HIIT would look like [11].

Although we know that fitter patients do better [4–7], and there is increasing evidence that we can improve preoperative oxygen consumption, we have not yet been able to consistently demonstrate that this improvement in preoperative cardiopulmonary fitness will result in a subsequent reduction in postoperative complications [25]. Although in some reviews this has been assumed to be the case, and the evidence for this is beginning to accumulate, this assumption needs to be properly tested. Initial evidence supporting this assumption included the ability for prehabilitation to reduce the risk of some complications such as chest infection [13] and some studies demonstrating a reduction in hospital stay [13, 26]. This evidence has now been strengthened by two recent studies, published after our study commenced, which were designed to look at clinical endpoints. One, a study on abdominal aortic aneurysms, demonstrated a significant reduction in a composite endpoint including cardiac, respiratory and renal complications [19]. The second, a study of patients undergoing major abdominal surgery, demonstrated that the number of patients experiencing any complication halved from 62% to 31% [27]. However, at the time of designing our RCT, most studies did not show a reduction in length of stay and very few studies had systematically examined postoperative complications. In the context of most centres not being able to perform a study large enough to use complications as the primary outcome, we were interested in assessing what the impact of improving oxygen consumption would be, not only on postoperative complications, but also on a range of other relevant clinical outcomes. These included hospital stay, recovery from surgery and quality of life. We also wanted to assess whether the impact would be the same for patients across a range of pathologies and surgical procedures.

We have therefore designed a prospective RCT comparing an exercise program using HIIT against standard preoperative care for patients undergoing major abdominal surgery. The overall objective of this study is to examine the impact of a focused individualised HIIT exercise program over a 4–6-week period on cardiopulmonary fitness and postoperative complications. The hypothesis that we will be testing is that an individualised and supervised preoperative HIIT program will result in a clinically significant increase in Peak VO_2_ of 2 mL/kg/min among those patients who adhere to the program. A second hypothesis, which we will gather information to help assess in future studies, is that a clinically significant increase in Peak VO_2_ will result in clinically relevant improvements in length of hospital stay, complications and time to return to normal level of functioning after surgery.

The aims of the current study are to:assess if an individualised and supervised preoperative HIIT program will result in a clinically significant increase in Peak VO_2_ of 2 mL/kg/min;better understand the practical issues of performing HIIT in the cohort of patients requiring major abdominal surgery, which will include frail elderly people with significant co-morbidities;examine the optimal individualization and delivery of HIIT to patients who are scheduled for major abdominal surgery; andassess the feasibility of performing a larger clinical outcomes study looking at the impact of preoperative HIIT. To do this, we will explore the best endpoint for a subsequent RCT by examining a range of clinical endpoints in our current study. The results of the study will help us to decide what will be the most appropriate endpoint for a subsequent study; the distribution of measurements for this endpoint will enable us to calculate the number of patients required to perform an appropriately designed and powered study. This will also help us to determine if a multi-centre study will be required.

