### Participant progress through the study

The study design is outlined in Fig. 1. In terms of patient care, all eligible participants have been assessed by their surgical team and by the hospital’s anaesthetic preassessment clinic. Potential participants for the study are identified when they are booked onto a list (with a specific date) for their operation. Those who are 4–6 weeks out from surgery, who live in or around Dunedin, and do not have any obvious exclusion criteria are contacted by the research nurse. Those who are interested are then invited to visit the hospital. Following discussion about the aims of the study and familiarisation with the study protocol, the participant is given written information about the study, is interviewed by the research nurse and is assessed by the study’s anaesthetist. When all questions are answered, and if there are no exclusion criteria, consent is obtained by the research nurse and the first cardiopulmonary exercise test (CPET) is performed. Baseline clinical data obtained before the CPET test includes full clinical history and examination, investigations done as part of the participant’s preoperative workup, up-to-date vital signs and a SF-36 quality of life score. The results of the CPET test are checked by a cardiologist and following this the participant is accepted into the study and randomly allocated 1:1 to standard care or to the exercise training group by the exercise physiologist. Randomisation was performed in blocks of unequal length (equal probabilities of 2, 4 and 6 lengths), using computerised sequence numbers generated in Stata, with no stratification. The allocation code is kept in sealed opaque envelopes which are sequentially opened. The allocation sequence was generated by the study statistician who has no involvement in the enrolment, assignment or assessment of participants. The enrolment of patients is coordinated by the research nurse. The number of patients approached, those excluded and those who declined to be involved (with reasons given for this) is also being documented as it the participant’s preference for exercise training or normal care.

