We selected a range of secondary outcomes to assess the potential impact HIIT may have on patient wellbeing, recovery from surgery and a range of clinical outcomes. Although the study is not powered for these endpoints, we hope to gain sufficient information about them to assist with the design of subsequent studies. The two traditional clinical outcome endpoints that we are assessing are the length of hospital stay and postoperative complications. The length of stay is the number of postoperative days stayed in hospital, with day 1 being the day of surgery. Postoperative complications, using standard definitions [32, 33], are documented in hospital and after discharge. Complications in hospital will be prospectively identified by visiting the patient in the ward and from the patient’s medical records. The patient will then be contacted by a member of the research team six weeks after surgery. A previously validated questionnaire [1] is used to identify complications that developed after discharge from hospital. We are also documenting three composite postoperative scores. The postoperative morbidity survey (POMS) assesses postoperative adverse events in nine different categories according to predefined criteria that are easy to check and to document [34]. This gives an excellent overview of postoperative morbidity [28] and may give a more comprehensive overview of postoperative difficulties than identifying specific postoperative complications. The questionnaire is performed on postoperative day 5, either by direct interview in the ward or by telephone if the patient has been discharged. In contrast, the surgical recovery scale (SRS) is designed to look specifically at recovery after surgery. This assesses 13 items including energy levels, feeling of fatigue and a number of practical physical activities, and correlates well with major complications and length of hospital stay [35]. The SRS will be performed on postoperative day 5 and will be repeated at six weeks as a postal questionnaire. Third, we are documenting the quality of life using the short form 36 health survey (SF-36). In the context of this study, the SF-36 has two purposes. The first is as a quality of life measurement tool to assess the impact of HIIT on the patients’ overall wellbeing. The second is to assess if there are any differences in physical function after surgery, which can be assessed by using the ten questions which make up the physical functioning component of the score. On the first occasion the SF-36 is completed it will be performed with the patient. On subsequent occasions it will be completed as a postal questionnaire.

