### Statistical methods for analysis of endpoints

Patient demographics will be described using appropriate descriptive statistics (mean and standard deviation for normally distributed continuous variables, median and interquartile range for other continuous variables, count and percentage for categorical variables). The main statistical analyses will be directed at answering per-protocol questions around whether 14 (on a per-protocol basis we will accept ten or more) training sessions is efficacious at improving conditioning before surgery and at improving postoperative outcomes compared to no training sessions. Additional analyses will investigate all patients who were randomised in an intention-to-treat analysis (as allocated and using imputed data as needed). Differences in changes of Peak VO2 (the primary outcome) and SF-36 scores between the HIIT and usual care groups will each be separately modelled using linear regression with adjustment for baseline values (mixed for SF-36 with a random patient effect to accommodate the repeated outcome measurements at week 6 and month 3 and an interaction between group and time). The models will also adjust for age, surgery type and ASA score. Linear mixed models will similarly be used for the surgical recovery scores (day 5 and week 6) with a random patient effect, interaction between group and time, and adjusting for surgery type and ASA score. Linear regression will be used to compare length of stay (days) between groups adjusting for surgery type and ASA score. Usual model diagnostics will be used (including checking normality and homoscedasticity of residuals) and where necessary natural logarithmic transformation of dependent variables or quantile regression to model medians will be used. Differences between groups in postoperative complications (yes/no) and day 5 postoperative morbidity scale (0–9 and dichotomised) will be compared using Poisson regression with robust standard errors, providing estimated relative risks, adjusting for surgery type and ASA score. Missing data will be replaced using multiple imputation for both the per-protocol and intention-to-treat analyses with chained estimating equations. Statistical analyses will be performed using R 3.4.1 or Stata 15.0 and statistical significance will be determined by two-sided *p* < 0.05.

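### The second hypothesis names time to return to normal functioning, but no outcome or analysis defines or times it, and the surgical recovery scale model omits the baseline function score the trial already collects

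*Protocol article*

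**What the plan says.** The Background introduces "A second hypothesis, which we will gather information to help assess in future studies", naming three outcomes that a rise in Peak VO2 should improve: "length of hospital stay, complications and time to return to normal level of functioning after surgery". The fourth aim in the same section is to choose the endpoint for a subsequent trial from the clinical endpoints examined here, and to size that trial from the distribution of the chosen endpoint.

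Two instruments bear on functioning after surgery:

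- **SRS.** Outcomes says: "The SRS will be performed on postoperative day 5 and will be repeated at six weeks as a postal questionnaire". Statistical methods for analysis of endpoints says: "Linear mixed models will similarly be used for the surgical recovery scores (day 5 and week 6) with a random patient effect", with "interaction between group and time, and adjusting for surgery type and ASA score".
- **SF-36.** Participant progress through the study lists, among the data taken before the first exercise test, "up-to-date vital signs and a SF-36 quality of life score". Outcomes says physical function after surgery can be assessed "using the ten questions which make up the physical functioning component of the score". The statistical section models SF-36 with adjustment for baseline and a random patient effect for the "repeated outcome measurements at week 6 and month 3".

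**The concern.** The hypothesis speaks of a time and of a return to normal. A reader would look for a definition of normal, an event or date of return, and an analysis that yields a time or something close to it. The protocol gives these for length of stay and complications but not for return to function.

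The instrument presented as the measure of recovery has no stated preoperative value, and its model contains no measure of function before surgery. The cohort is expected to vary widely. The Background foresees frail older patients with serious co-morbidity, Interventions plans for physiologically fit participants, and the Discussion reports that some of those enrolled had been inactive or in poor health. The same week 6 SRS score can therefore mean full recovery in one patient and partial recovery in another.

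Two things are at stake. Return to function could reach the endpoint-selection stage without a defined summary, and so could not be compared with the other candidates. The SRS comparison would also carry variation that a baseline score already on file could partly explain.

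**Working it through.** The plan states no figure for this construct, so the check is to set the sections side by side.

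**1. Hypothesis against outcomes**

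| Named in the second hypothesis | Defined in Outcomes? | Analysis in the statistical section? |
|---|---|---|
| Length of stay | Yes, postoperative days with the day of surgery as day 1 | Yes, linear regression |
| Complications | Yes, standard definitions, in hospital and at six weeks | Yes, Poisson regression with robust standard errors |
| Time to return to normal functioning | No | No |

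**2. What the measurements can show about return**

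| Instrument | Stated preoperative values | Postoperative values | What can be said about return |
|---|---|---|---|
| SRS | 0 | 2 (day 5, week 6) | No comparison with the patient's own preoperative level |
| SF-36 physical functioning | 1 (baseline) | 2 (week 6, month 3) | Back to baseline by week 6, between week 6 and month 3, or not by month 3 |

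The schedule figure (Fig. 2) is not shown, so a preoperative SRS there cannot be excluded. The three sections in which it would be expected mention none.

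**3. Covariates in the models**

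| Model | Baseline value | Age | Surgery type | ASA score |
|---|---|---|---|---|
| Peak VO2 | Yes | Yes | Yes | Yes |
| SF-36 | Yes | Yes | Yes | Yes |
| SRS | None listed | Not listed | Yes | Yes |

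The word 'similarly' in the SRS sentence might be read as carrying over the baseline adjustment. That sentence gives its own covariate list, however, and there is no stated baseline SRS to carry over.

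**4. Is the omitted covariate legitimate?** The baseline SF-36 is completed before the first exercise test, and randomisation follows that test. The score is therefore free of any treatment effect. The Discussion supports such adjustment in principle: it justifies the surgery type and ASA terms by the unexplained variance they remove and the chance imbalance they correct.

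**5. Size of the gain.** Let r be the correlation of baseline SF-36 physical functioning with SRS at a given time point, after allowing for surgery type and ASA score. Adding the score multiplies the residual variance at that time point by about (1 − r²), at the cost of one degree of freedom. It has to be this partial correlation, because ASA score already carries part of the preoperative health status. The document gives no value for r, so no percentage follows. The trial's own data will allow r to be estimated.

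**The case against.** The strongest reply is that the hypothesis is deferred. The Background leaves it to future studies, Outcomes disclaims power for the secondary endpoints, and time to return is not itself a declared outcome. No declared endpoint therefore lacks its measurement. This stands and lowers the weight of the point. It does not remove it: the trial undertakes to gather information on this hypothesis and to select the next endpoint, and for one of the three named outcomes nothing is specified to be gathered.

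A reader might infer that the trial cannot tell whether patients return to normal at all. The document does not support that. SF-36 physical functioning is taken at baseline, week 6 and month 3, is modelled with baseline adjustment, and is expressly meant to show differences in physical function after surgery. What is missing is the timing, beyond coarse intervals, and a stated return-to-function summary.

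A reader might also infer that the absent baseline SRS biases the comparison between arms. It does not. Under randomisation a missing baseline covariate mainly costs precision, and the difficulty of comparing a frail patient with a fit one concerns individual scores, not the contrast between groups.

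Finally, it is tempting to say that a next trial sized on this SRS variance would be too large by some percentage. That would need the unknown partial correlation. It would also hold only if the next trial collects and adjusts for a baseline functional score; for a trial that does not, the variance observed here is the right one for planning.

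An extra covariate is often left to the analysis plan, which is not shown. The protocol does, however, state the SRS covariates explicitly, so the comment is on what it fixes.

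**Conclusion.** The point holds in limited form. The timing construct in the second hypothesis has no matching outcome or analysis, and the SRS model as stated leaves out a prognostic score that the trial already holds. The first is a mismatch of wording and specification in a deferred hypothesis. The second is an avoidable loss of precision, not a bias.

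The size of that loss is unknown and should not be given as a figure. The conclusion assumes that Fig. 2 contains no preoperative SRS, and that baseline physical functioning is related to SRS beyond what surgery type and ASA score explain. The second assumption is plausible in this mixed cohort but is not shown in the document.

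Baseline is also not the same as normal, because it is taken in patients already awaiting surgery for their disease. This is a further reason to reword the hypothesis.

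**What to change.** 1. Add baseline SF-36 physical functioning as a covariate in the SRS mixed model. The data are already collected; the cost is one degree of freedom. Make the change before the statistician is unblinded.
2. Report change from baseline in SF-36 physical functioning, with its spread, by arm at week 6 and month 3, and name it as the return-to-function measure to be weighed in choosing the next trial's endpoint. The measurements and the baseline-adjusted SF-36 model already exist, so this is one further summary. Keeping the score continuous avoids a cut-off at the patient's own baseline, where measurement error alone can put a recovered patient just below the line.
3. Reword the hypothesis from time to return to normal functioning to recovery of baseline functioning by week 6 and month 3, which is what the schedule can show.

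A preoperative SRS could be started for later participants, but enrolment began in September 2015, so it would cover only part of the trial and add little. When the trial reports, it would help to give the observed partial correlation of baseline physical functioning with SRS, so that those planning the next study can judge the gain for themselves.
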